## Abstract

**Background:**

Novel host-directed therapies are urgently needed for patients with dengue, particularly those at high risk of developing severe disease. Broad immunosuppression using corticosteroids in unselected patients with dengue has so far been unsuccessful. Patients with hyperinflammation (raised CRP and/or ferritin levels) are at highest risk of poor outcomes in dengue. Anakinra is a licensed, bio-engineered form of the naturally occurring IL-1R antagonist which has shown efficacy in other acute viral-associated hyperinflammatory syndromes.

**Methods:**

This is a randomized placebo-controlled phase II trial of anakinra in 160 patients ≥ 12 years old, diagnosed as having dengue with warning signs or severe dengue and the hyperinflammatory syndrome (plasma ferritin >2000 ng/ml). Participants will receive a 4-day course of either anakinra or placebo. The primary endpoint is the efficacy of anakinra measured by the delta mSOFA score* (change in mSOFA score over 4 days after randomization). The accompanying immunological and transcriptomic analyses aim to identify novel mechanisms and pathways that may represent future biomarkers and therapeutic targets.

**Discussion:**

The observed immunomodulatory benefit of anakinra in acute viral-associated hyperinflammatory syndromes including COVID-19 and auto-immune diseases makes this medication a promising potential treatment for dengue patients with hyperinflammation. This trial will assess the safety and efficacy of anakinra in patients with severe dengue or at high risk of developing life-threatening dengue disease.

**Registration:**

ClinicalTrials.gov (NCT05611710).

## Background

Dengue continues to be a major public health burden in Vietnam and globally
^
1
^. While most clinical cases of dengue resolve after 1 week, approximately 5–10% of hospitalized patients will develop severe manifestations, usually during the critical phase (day 4–6 of illness)
^
2
^, allowing a window of opportunity to identify patients at risk of progression and intervene with a disease modifying agent
^
3,
4
^. However, thus far, no antiviral agents or adjunctive therapies have been found to alter disease outcomes in dengue
^
3–
6
^. Novel host directed therapeutics are urgently needed for patients with dengue, particularly those at high risk of developing severe disease.

Understanding of the mechanism underlying progression to severe disease has improved; it has been demonstrated that hypercytokinemia and an excessive host inflammatory response to infection are associated with life-threatening complications
^
2,
3
^. The dengue virus (DENV) replicates within monocytes and macrophages, and failure to clear these virus-infected cells by dysfunctional cytotoxic NK/CD8+ T cells can facilitate a hyperinflammatory state or “cytokine storm”, through persistent macrophage activation and ultimately end-organ damage. Therapeutic trials with broad immunosuppression using corticosteroids in dengue have so far been unsuccessful
^
5
^, likely due to unselected patient populations with insufficient stratification. Interleukin-1 (IL-1) is a key pro-inflammatory cytokine involved in the cytokine storm and also in dengue pathogenesis
^
7–
9
^. One of the safest and possibly most targeted ways of controlling this excessive inflammation is through IL-1 receptor (IL-1R) blockade
^
6
^.

### Anakinra

Anakinra is a licensed, bio-engineered form of the naturally occurring IL-1R antagonist that blocks the action of IL-1. Clinical trials have shown efficacy of anakinra in reducing adverse outcomes in other acute viral-associated hyperinflammatory syndromes, including COVID-19
^
10–
12
^. This drug has already been licensed in various countries and is currently used to treat signs and symptoms of rheumatoid arthritis, cryopyrin-associated periodic syndromes, familial Mediterranean fever, Still’s disease and COVID-19
^
13
^.

In dengue, a recent publication reported experience of administering anakinra intravenously, in addition to intravenous methylprednisolone and intravenous immunoglobulins, to a returning traveller with severe dengue and a recent diagnosis of systemic lupus erythematosus, who had clinical, biochemical and bone marrow features consistent with secondary haemophagocytic lymphohistiocytosis (HLH). Initiation of anakinra was followed by resolution of the HLH markers and reduced requirements for multi-organ support
^
14
^.

### Cytokine storm and inflammatory biomarkers

Previous studies have shown that features of Macrophage activation syndrome (MAS)/secondary HLH/hyperinflammation are more prevalent in severe dengue. Higher inflammatory biomarkers, including higher ferritin
^
8,
9,
15
^ and an early higher peak plasma IL-1R antagonist (IL-1RA) levels (a surrogate for IL-1 activity)
^
7
^, are associated with more severe clinical outcomes in dengue. In a cohort of 207 hospitalized dengue patients (children and adults) in Vietnam, 63% with severe disease and 33% with moderate disease had ferritin levels > 2000 ng/ml ([name], unpublished data). In another cohort of 135 adults with dengue shock in Ho Chi Minh City, median plasma ferritin measured within 24 hours of shock onset was 7671 ng/ml, but among those who did not survive their illness, median plasma ferritin was 71,573 ng/ml at enrolment, and 100,000 ng/ml 48 hours later
^
16
^.

While measurement of IL-1 activity is complicated due to low concentrations, local production and short half-life
^
7
^, ferritin testing is readily available in clinical practice. In this trial, we propose using ferritin as a screening biomarker to identify patients at high risk of severe and life-threatening dengue, in whom immunomodulation may improve clinical outcomes.

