### Primary endpoint

The primary endpoint of this study is the delta mSOFA score* (change in mSOFA score over 4 days after randomization).

*mSOFA = modified Sequential Organ Failure Assessment score (modified for resource limited settings and dengue) see Appendix 1 for score.

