### Screening

Patients hospitalized to one of the study wards of the Hospital for Tropical Diseases (HTD), Ho Chi Minh City, Vietnam with clinically suspected dengue with warning signs/severe dengue will be identified and, if potentially eligible, approached by study staff. If patients agree to participate in the trial and provide the written consent/assent form, they will be screened for eligibility based on the criteria listed in the section above. Initial screening tests include baseline ferritin, creatinine, HBsAg and, in all female patients, a pregnancy test using a urine dipstick.

Potentially eligible patients who have baseline ferritin levels > 1000 ng/ml but ≤ 2000 ng/ml on admission will be invited to continue the screening phase of the trial which lasts for 3 days with daily ferritin testing. If the ferritin level rises to above 2000 ng/ml during this period, and all inclusion criteria are met, the patient will be recruited. If the ferritin remains below the 2000ng/ml threshold after 3 days, the screening phase will end and all study procedures will stop. Patients will also be excluded if their ferritin levels are below 1000ng/ml.

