### Statistical considerations

**
*Sample size.*
** Given that delta mSOFA score has an approximately normal distribution
^
25
^ with a standard deviation of 2.4, which was based on a cohort of 38 adults admitted with severe dengue, we would need a sample size of 80 patients per group to detect a between-group difference of at least 1.0 point with 80% power and 5% type-I error rate.

**
*Statistical analysis.*
** The primary endpoint (delta mSOFA score) and the secondary endpoints (ALT, CRP, PLTs and ferritin) will be analyzed using a linear mixed-effects model, which models their values over the first 4 days for mSOFA and 5 days for lab tests (as specified in sections 2.4.1 and 2.4.2). We will use a linear trend for time as fixed and random effects. The slope of this model reflects the change in value over time. Therefore, the effect of anakinra is measured as the difference in slope between treatment groups. This difference will be assessed via the interaction between time and treatment group in that model, and presented with a corresponding 95% confidence interval. For the change at day 30 (ferritin and CRP) we will use the difference with the value at randomisation. Mortality will be assessed by comparing Kaplan-Meier curves via log-rank test. The number of serious adverse events will be compared via 2×2 tables with chi-square tests, or Fisher’s exact test in case the expected number under the null hypothesis is smaller than 1 in at least one of the cells. Number of AEs per individual will be compared using Poisson regression, or quasi-Poisson regression in case of overdispersion. EQ visual analogue score will be compared via linear regression in case it has a fairly symmetric distribution; otherwise we will use beta-regression. Normalization of neutrophils will be defined as first time to reach normal range of >2.0 ×10
^9^/l and for platelets the first time to reach >150 ×10
^9^/l and will be assessed by Cox model. For viraemia AUC and duration outcomes we will also perform the analysis with correction for day of illness (DOI). The time of fever clearance is defined by the first time after which all readings are <37.5°C in the following 48 hours.

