## Discussion

Dengue remains a major global public health burden. Over the last few decades, the geographic distribution of the Aedes mosquito vector has been expanding and dengue cases have been increasing; the increasing incidence is predicted to continue with ongoing urbanization, demographic shifts and climate change
^
26,
27
^. Despite the increasing burden, there are currently no approved treatments to either reduce viral replication or to modify the deleterious host inflammatory response to infection. Development and investigation of novel therapeutics has been slow due to disinterest in this historically neglected tropical disease. 

Like other acute viral infections, including Ebola, SARS-CoV2 and influenza, severe dengue is associated with an excessive host inflammatory response presenting in the critical phase of disease (usually days 4–6 of infection). High IL-1, ferritin, and C-reactive protein are all associated with severe dengue
^
15,
28–
30
^. In particular, ferritin has emerged as a useful prognostic biomarker; higher ferritin is associated with increased risk of disease progression, higher SOFA score, need for intensive care admission and mortality
^
16,
28
^.

Until recently, the mechanistic basis for hyperferritinaemia and hyperinflammation in dengue hasn’t been well understood, but recent insights suggest that it occurs due to a combination of unchecked viral replication within macrophages and monocytes, with viral uptake mediated by non-neutralising antibodies from prior infection with a heterotypic dengue serotype, in addition to dysfunctional NK T cells with impaired cytolytic function with reduced perforin and granzyme B production
^
19
^.

As an IL-1 receptor antagonist, Anakinra targets the IL-1β hyperinflammatory loop which mediates hyperferritinaemia, coagulopathy, fever and tissue damage. Anakinra improved survival in a subgroup of patients with sepsis-associated hyperinflammation (ferritin >2000 ng/mL, coagulopathy, and liver enzyme elevations)
^
31

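### The primary mSOFA slope model names no baseline covariate; prespecifying log ferritin and its interaction with time would probably gain some precision at almost no cost.

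*Protocol article*

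**What the plan says.** **Endpoint and model.** The Primary endpoint section states: "The primary endpoint of this study is the delta mSOFA score* (change in mSOFA score over 4 days after randomization". Statistical considerations analyses it with a linear mixed-effects model over the first 4 days: "We will use a linear trend for time as fixed and random effects". The treatment effect is the difference in slope, read from the time-by-treatment interaction. No baseline covariate is named for this model. The only covariate adjustment in that section is day of illness, for the viraemia AUC and duration outcomes.

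**Ferritin.** Inclusion and exclusion criteria require a value above 2000 ng/ml and state no upper limit. The Screening section says: "Initial screening tests include baseline ferritin, creatinine, HBsAg". Patients between 1000 and 2000 ng/ml may be retested daily for 3 days and enter if they cross the threshold. Every participant therefore has a value before randomisation. The Discussion says that "higher ferritin is associated with increased risk of disease progression, higher SOFA score, need for intensive care admission and mortality". The background section on cytokine storm and inflammatory biomarkers reports, for 135 adults with dengue shock, a median of 7671 ng/ml overall, and that "among those who did not survive their illness, median plasma ferritin was 71,573 ng/ml at enrolment".

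**Allocation.** The Design and Randomization sections give 1:1 minimisation, stratified by ward of recruitment (intensive care or emergency department versus general dengue wards). Ferritin is not an allocation factor.

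**The concern.** The article treats ferritin as informative enough to decide who enters the trial, and links it to SOFA, the score from which the primary endpoint is derived. Entry has no ceiling, and in the shock cohort the median of the patients who died was 71,573 / 7671 = 9.3 times the cohort median. So the marker can still separate patients well above 2000 ng/ml.

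If ferritin predicts how mSOFA moves over the 4 days, leaving it out keeps that predictable variation in the standard error of the treatment effect. This matters more here because, on the stated inputs and a two-sided test, the planned size gives less than 80% power before any adjustment.

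**Working it through.** **Inputs, all from Statistical considerations.** SD of delta mSOFA: "with a standard deviation of 2.4, which was based on a cohort of 38 adults admitted with severe dengue". Target: "to detect a between-group difference of at least 1.0 point with 80% power and 5% type-I error rate". Size: "we would need a sample size of 80 patients per group". The article does not state whether the test is one- or two-sided; the planned 95% confidence interval fits two-sided, which is used here.

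**Step 1: the plan's own figure.**

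- n per group = 2 × (1.960 + 0.842)² × 2.4² / 1.0² = 90.4, so 91 (92 with the noncentral t).
- SE with 80 per group = 2.4 × √(2/80) = 0.379.
- Power = Φ(1.0/0.379 − 1.960) = 75.0% (74.5% with the noncentral t).

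The stated 80 per group is not reproduced two-sided. A one-sided 5% test needs 72, and 72/0.90 = 80 with 10% dropout, but the article states neither. That mismatch is a separate matter. Here it only sets the starting point of 75.0%.

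**Step 2: effect of adjustment.** Let r be the within-arm correlation between log ferritin at randomisation and change in mSOFA. The documents do not give r, so a range is assumed. Residual SD = 2.4 × √(1 − r²), put back into the formulas of step 1.

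| Assumed r | Residual SD | SE (80 per group) | Power | n per group for 80% |
|---|---|---|---|---|
| 0 (unadjusted) | 2.400 | 0.379 | 75.0% | 91 |
| 0.1 | 2.388 | 0.378 | 75.4% | 90 |
| 0.2 | 2.352 | 0.372 | 76.7% | 87 |
| 0.3 | 2.289 | 0.362 | 78.9% | 83 |
| 0.4 | 2.200 | 0.348 | 82.0% | 76 |

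In equivalent patients, 1/(1 − r²) − 1 gives 1.0%, 4.2%, 9.9% and 19.0% for r = 0.1 to 0.4. Power reaches 80% with 80 per group when the residual SD is 2.257, that is r² = 1 − (2.257/2.4)² = 0.115, or r of about 0.34.

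**Step 3: chance imbalance.** The part of the unadjusted estimate that comes from chance ferritin imbalance has SD r × 0.379. At r = 0.3 this is 0.114 points, with a 95% range of ±1.96 × 0.114 = ±0.22. It is not an additional error: 0.362² + 0.114² = 0.131 + 0.013 = 0.144 = 0.379². The imbalance is exactly the variance that adjustment removes, and the unadjusted 95% interval of ±1.96 × 0.379 = ±0.74 already contains it.

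**Step 4: which term is needed.** The estimand is a difference in slopes. A ferritin main effect shifts a patient's whole trajectory and leaves the slope contrast untouched. A small simulation checked this: 60 runs, 80 per group, daily scores on days 0 to 4, random intercept and slope, and an assumed correlation of 0.4 between ferritin and slope. The mean SE of the slope difference was:

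- no ferritin: 0.1016
- ferritin main effect only: 0.1016
- ferritin and ferritin-by-time: 0.0945

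Only the interaction with time helps: 0.0945/0.1016 = 0.93, a 7% smaller SE.

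**The case against.** **The covariate list may be in the analysis plan.** The article does not say that covariates are excluded, and the full analysis plan is not shown. A reader might infer that the trial has ruled adjustment out; the text does not support that. What remains is that the article does fix the time terms and the effect measure, and names a covariate where it plans one, for the viraemia outcomes. A recommendation on the stated model is fair. If the analysis plan already includes ferritin, the two texts only need aligning.

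**The evidence concerns something else.** The cited associations are with SOFA level, severity, intensive care need and death. None is with the 4-day change in mSOFA among patients already above 2000 ng/ml, and a link with level does not establish a link with slope. This stands: the gain is plausible but not shown.

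**Ward stratification may already help.** The article ties ferritin to intensive care need, and reports values above 2000 ng/ml in 63% of severe against 33% of moderate cases. Stratifying by ward may therefore partly balance ferritin. This also stands, and it makes the imbalance figure in step 3, which assumes no such balance, an upper indication.

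**The spread at entry is unknown.** A reader might infer that enrolled values run up to 100,000 ng/ml. That figure is the median in non-survivors 48 hours after enrolment in the shock cohort. It is not an entry value, and a shock cohort does not describe a trial that also recruits general-ward patients with warning signs.

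**The arithmetic is a two-sample approximation.** It treats delta mSOFA as one change score, as the plan's own sample size does, and not as a slope from repeated measures. The direction carries over; the exact percentages may not.

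**Conclusion.** The point holds as an efficiency improvement. The primary slope model names no baseline covariate, although a marker that the article itself calls prognostic is measured before randomisation in every participant. Precision is probably forgone, but the amount is unknown. It is under 2 percentage points of power if r is 0.2 and about 7 if r is 0.4. The documents neither support nor exclude a value as high as the 0.34 at which adjustment alone would bring power to 80%.

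A reader might go further and infer that chance ferritin imbalance biases the primary result or makes it unreliable. It does not: allocation is randomised, and the unadjusted estimate and its interval are valid. Lost precision and chance imbalance are one variance component and should not be counted as two harms.

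These conclusions rest on the stated SD of 2.4, a two-sided 5% test, the normal approximation, 80 analysed per group, and an assumed r.

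**What to change.** Before unblinding, prespecify in the primary mSOFA model two further fixed effects: log-transformed ferritin at randomisation, and its interaction with time. Keep the time-by-treatment interaction as the treatment effect. Define the covariate as the last value before randomisation, because patients who entered after daily retesting also have an earlier value at or below 2000 ng/ml. Report the model without ferritin as a sensitivity analysis. If the analysis plan already contains these terms, make the protocol text agree with it.

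The cost is at most two extra parameters in 160 patients, with no new data and no more participants. Adjusting for a prespecified pre-randomisation covariate in this linear model preserves the type I error. If ferritin proves unrelated to the slope, almost nothing is lost. Recruitment began in January 2024, so the choice should be dated and fixed soon; adding the term after unblinding would look data-driven.

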### Cellular immunology

Cytotoxic NK/CD8+ T cells are involved in the control of macrophage activation and direct killing of virus-infected cells. Dysfunctional NK/CD8+ T cells underlie hyper-inflammatory phenotypes; resulting in uncontrolled macrophage expansion and activation that augments and prolongs the release of pro-inflammatory cytokines. NK cell cytotoxic ability correlates with effective dengue viral clearance and better clinical outcomes
^
17
^. In CD8+ T cells, selective loss of cytotoxic function is proposed to cause an imbalance in the negative feedback loop of antigen presentation and cytokine secretion. The subsequent inappropriate expansion of this cell type leads to excessive production of T-cell–derived cytokines, resulting in histologic and clinical features of HLH
^
18
^. We have shown that patients with severe dengue have a lower percentage of activated and proliferating NK cells and lower expression of the cytotoxic granules perforin and granzyme B when compared to patients with less severe dengue infection
^
19
^. 

Monocytes and macrophages are the main target cell for dengue viral replication and a major source of inflammatory cytokines. Macrophages are involved in all stages of the inflammatory process, polarized by their environment to have inflammatory initiation and propagation (M1) or resolution (M2) or mixed functions. An imbalance of M1/M2 macrophages may induce pathological consequences, from excessive inflammatory mediators or an inadequate production of resolution mediators
^
20
^. The association between macrophage polarization phenotypes and disease outcome in dengue, however, is largely unknown. We hypothesize that switching off the cytokine-mediated hyperinflammatory loop with IL-1R blockade will restore T/NK cell and M1/M2 homeostasis and prevent downstream tissue damage.

### Genetic associations

Genetic polymorphisms may alter the NK cell cytotoxicity pathway and create hyperinflammatory phenotypes upon immune activation, triggered by various infections. Some of these genes, including those encoding perforin and proteins required for movement and fusion of perforin-containing granules, are well described in MAS
^
21
^. Further support for a possible key role of NK cells is provided by a genome-wide association study by our group that identified an association between a polymorphism in MICB (an NK cell-activating ligand) and dengue severity
^
22
^. We assessed the association of these known and novel NK cell single nucleotide polymorphisms (SNPs) with disease severity. Confirmation of these novel SNPs in a different cohort is required.

Overall, we consider that data demonstrating that the hyperinflammatory phenotype is associated with severe dengue, and that the phenotype is associated with underlying dysfunction of cellular immunity and specific NK cell SNPs is sufficient to move forward with a trial of immunomodulation
^
19,
22
^. 

We plan to investigate genetic signatures in specific immune cell subsets over the disease course in the trial patients, assessing differences with clinical outcomes and IL-1R blockade. We will assess the gene expression profile from NK and CD8+ T cells (which will address the confounding influences of unseparated cells) at two time-points: enrolment and day 5 following anakinra or placebo. Transcriptomic profiling will provide further understanding of the pathogenic pathways in patients with dengue and the effect of therapeutic IL-1R blockade on these pathways.

